# Efficacy of combined orthokeratology and 0.01% atropine for myopia control: the study protocol for a randomized, controlled, double-blind, and multicenter trial

**DOI:** 10.1186/s13063-021-05825-1

**Published:** 2021-12-01

**Keywords:** Myopia control, Orthokeratology, 0.01% atropine, Pediatrics, Multicenter trial

## Abstract

**Background:**

The prevalence of myopia is increasing worldwide and is presently recognized as a major public health issue. Researchers and clinicians have been devoted in exploring appropriate clinical interventions to slow its progression in children. Mounting publications have proven that both orthokeratology (OK lens) and 0.01% atropine eyedrop can retard eye growth and myopia progression. However, it remains unclear whether the combination of OK lens and 0.01% atropine has the potential to magnify the effectiveness of myopia control. The present study aims to compare the myopia control efficiency of the combination of OK lens and 0.01% atropine with the monotherapy of OK lens in children.

**Methods:**

The present study is a randomized, controlled, double-blind and multicenter clinical trial. A total of 96 children within 8–12 years old were recruited. These participants are treated with the combination of OK lens and 0.01% atropine eyedrop or the combination of OK lens and placebo eyedrop. Each group includes 48 participants. The inclusion criteria are as follows: myopia between − 1.00 and − 4.00 D in either eye and astigmatism of no more than 1.50 D. The follow-up time points will be 1, 6, 12, 18, and 24 months from randomization. The primary outcome is determined by the difference in axial length of the two groups, between the baseline and 24 months from randomization.

**Discussion:**

The present randomized, controlled clinical trial would indicate the additive effects of the combination of OK lens and 0.01% atropine, and the extent of these effects, in retarding myopia progression and axial elongation in children.

**Trial registration:**

Chinese Clinical Trial Registry (ChiCTR), ChiCTR1800018419. Registered on 17 September 2018. http://www.chictr.org.cn/showproj.aspx?proj=29216

**Supplementary Information:**

The online version contains supplementary material available at 10.1186/s13063-021-05825-1.

## Background

The prevalence of myopia is dramatically increasing, worldwide, especially in East Asia [1]. Recent studies have indicated that the prevalence of myopia in East Asian countries has reached as high as 90% [2]. It is estimated that there will be approximately five billion people (half of the world’s population) with myopia by 2050 [1]. In addition, myopia occurs at younger ages. A number of studies have presented that children who develop myopia at a younger age is prone to progress more quickly and ultimately progress to high myopia [3, 4]. Myopia progression is usually accompanied by the elongation of the axial length, which may result in vision-threatening pathology, such as macular degeneration, retinal detachment, and glaucoma [5, 6]. Given the high prevalence of myopia and its strong association with sight-threatening ocular diseases, myopia has become a major public health concern. Hence, it is critical to explore effective strategies to control myopia progression.

At present, numerous studies have assessed the efficacy of OK lens and atropine for myopia control in children [7–9]. OK lens was originally designed to correct myopia and provide clear unaided visual acuity during the day. At present, increasing evidence has shown that OK lens is effective for slowing axial elongation and myopia progression. A single-masked randomized clinical trial conducted in Hong Kong revealed that the increase in axial length in the OK lens group was less than that in the single-vision spectacle glasses group (0.36 mm vs. 0.63 mm) at 2 years [7]. In the cohort study conducted in Japan, the increase in axial length for over 2 years was 0.39 mm and 0.61 mm in the OK lens and the single-vision spectacle glasses groups, respectively [8]. In a retrospective cohort study conducted in China, the OK lens group exhibited less changes in axial length, when compared to the single-vision spectacle glasses group, at 2 years (0.34 mm vs. 0.70 mm) [9]. In conclusion, OK lens can induce a 40–60% mean reduction in axial elongation, when compared to single-vision spectacles, in terms of correcting myopia, at present.

Other than OK lens, topical atropine therapy has also been demonstrated to be effective in retarding myopia progression in children. High-dose atropine (1% and 0.5%) and moderate-dose atropine (0.1%) have been shown to have a dose-dependent retardation effect [10, 11]. However, these doses usually induced photophobia side-effects during treatment, which resulted in a high dropout rate [11, 12]. In addition, the rebound effect after atropine discontinuation has been reported, and this was especially notable in higher concentrations of atropine [13]. Recently, several studies have reported that 0.01% atropine is effective for slowing myopia progression, with negligible side-effects [14, 15]. The 5-year study of atropine treatment for myopia (ATOM2) revealed that for the myopia progression of 0.01% atropine, in terms of refraction, this was found to have a similar efficacy as that of 0.5% and 0.1% atropine at the end of 2 years [16]. After the “wash-out period” of the third year, the overall progression of myopia in the 0.01% atropine group was significantly lower than that of the 0.5% and 0.1% atropine groups. Then, the study continued to restart the 0.01% atropine for two further years. At the end of 5 years, the overall progression of spherical equivalence myopia in the 0.01% atropine group was significantly lower, when compared to the 0.1% and 0.5% atropine groups. Despite the encouraging overall results of the ATOM2 study, not all participants responded well to atropine. In the ATOM2 study, 9.3% of children in the 0.01% group had myopia progression of ≥ − 1.5 D over the initial 2-year treatment. This was higher than that in the 0.5% and 0.1% groups. However, in the LAMP study, the use of 0.01% atropine had a minimal effect in controlling the myopia progression and axial elongation over 1 year [17]. In addition, spectacle lenses or contact lenses are needed during the daytime, since atropine solutions cannot correct the myopia.

The exact mechanism of the myopia control of OK lens or atropine eyedrop is presently not fully understood. Recently, OK lens is known to control myopia progression by reducing the peripheral hyperopic defocus [18]. Atropine is thought to have effects on anti-muscarinic receptors of the retina and sclera [19]. Chen et al. reported that large pupil diameters can facilitate the effect of OK lens to slow axial growth in myopia [20]. In addition, 0.01% atropine eyedrop were proven to have a significant increase in pupil size [21]. Thus, the combination of OK lens and 0.01% atropine treatment may have great potential in magnifying the effectiveness of myopia control. In a previous randomized clinical trial conducted in Japan, the combination therapy was more effective in slowing axial elongation than monotherapy of OK lens over the 2 years (0.29 mm vs. 0.40 mm) [22]. Pauline and his colleagues set a randomized, observer-masked, prospective study in Hong Kong [23]. They found the additional use of 0.01% atropine did not affect the OK lens performance or clinical responses after 1 month of treatment [23]. The possible synergistic effect of combination treatment for myopia control needs longer study duration. However, these studies were not masked to the participants, and the control group only receives OK lens treatment without placebo eyedrop. Thus, we conducted a randomized, controlled, double-blind and multicenter trial to investigate the additive effects of the combination of OK lens and 0.01% atropine eyedrop in slowing axial elongation in children with myopia.

## Methods/design

The present prospective, multicenter, randomized controlled, double-blind clinical trial aimed to evaluate the efficacy of the combination of OK lens and 0.01% atropine for the treatment of childhood myopia. The clinical trial is presently being undertaken in Shanghai General Hospital, Wenzhou Medical University, and Zhongshan Ophthalmic Center, Sun Yat-sen University, China. The trial is being coordinated by Shanghai General Hospital. Ethical approval was obtained from the Institutional Review Board of Shanghai General Hospital, Wenzhou Medical University, and Zhongshan Ophthalmic Center, Sun Yat-sen University. Written informed consent was collected from the participants and their parents/guardians prior to the enrolment. The schedule of enrolment, intervention, data collection, and assessment conform to the Standardized Protocol Items: Recommendations for Interventional Trials (SPIRIT) guidelines (Table 1, Additional file 1). The study flow schedule is shown in Fig. 1.

**Table 1 Tab1:**
[figure not shown]
Standard Protocol Items: Recommendations for Interventional Trials (SPIRIT)

**Fig. 1 Fig1:**
[figure not shown]
Study flow diagram

### Participant eligibility

#### Inclusion criteria

The participants were within 8–12 years old. These participants intended to undergo the OK lens treatment. The inclusion criteria for the present study were as follows: spherical equivalent refractive error between − 1.00 and − 4.00 D in either eye, astigmatism of no more than 1.50 D in either eye, a best corrected visual acuity (BCVA) of no worse than 25/25 in both eyes, the weight of birth was no less than 1500 g, the patient/guardian agrees to be randomized, and attends the scheduled and follow-up visits.

#### Exclusion criteria

The exclusion criteria were as follows: patients with ocular disorders, such as strabismus, amblyopia, cataract, or ptosis; patients previously used OK lens or atropine eyedrop to prevent myopia progression; patients with disorders contraindicated to atropine, such as known allergies, cardiovascular disease, or epilepsy; patients with disorders contraindicated to OK lens wear, such as ocular inflammation or infection; and patients with systemic disorders that might affect refractive development, such as Down syndrome or Marfan’s syndrome.

### Randomization and masking

A statistician was responsible for the randomization of the 0.01% atropine eyedrop or placebo eyedrop, which was achieved using a web-based randomization program. The randomization was stratified by center with fixed block size of 4. Cards that identified the combination of OK lens and 0.01% atropine group and OK lens group were placed in sealed opaque envelopes and kept by the principal investigator until the conclusion of the trial. The principal investigator should open the opaque envelopes in an emergency.

The 0.01% atropine eyedrop and placebo eyedrop were prepared in a manner that appeared similar in appearance. The manufacturer of the eyedrop labeled the investigational eyedrop according to the randomization code number. Then, the manufacturer delivered the pre-randomized eyedrop to each recruitment center. The masked investigator was responsible for the ophthalmic measurements but was not allowed to handle the eyedrops throughout the study. During the clinical trials, neither the participants nor the masked investigator were aware of the group allocation. The masked clinical research coordinator (CRC) guided the participants in performing and finishing each of the examinations. All outcome assessments were performed by masked investigator.

### Recruitment

Participants were recruited from outpatients at each study site. The potentially eligible participants and their parents or guardians were contacted by CRC. And the CRC introduced the study to the participants and their parents or guardians in detail. The interested participants and their parents or guardian were invited to perform a screening examination to assess their eligibility. At the enrolment visit, the participants and their parents or guardian signed the informed consent before the examination.

### Intervention

Eligible participants were randomly assigned to the combination of OK lens and 0.01% atropine group, or the combination of OK lens and placebo eyedrop group, at a 1:1 ratio. Participants were recruited from 3 hospitals in China. To ensure balance in study site, a stratified and block randomization algorithm was used and randomization was stratified by study site and block sizes of four were used within each strata. The 0.01% atropine and placebo eyedrop looked identical in the appearance and was labeled according to the randomization code number. The participants got the eyedrop that corresponded to the assigned consecutive number in accordance with their entrance to the study.

The treatment for the combination of OK lens and 0.01% atropine group comprised of the instillation of one drop of 0.01% atropine in each eye, at 10 min before OK lens insertion, and at least 8 h of overnight wear of OK lens. Participants in the OK lens group wore the OK lens every night after the placebo eyedrop instillation. Under the condition of illness or the presence of any abnormal ocular symptoms, the nightly wear of the OK lens and use of the atropine or placebo eyedrop would both be suspended. Follow-up visits were performed at 1, 6, 12, 18, and 24 months from randomization. We provided the 3-month dosage of 0.01% atropine eyedrop or placebo eyedrop at a time. The parents or guardians are required to return the consumed vials to the investigator every 3 months. The eyedrops were being sent to minimize dropouts during the pandemics.

### Primary outcome

The primary outcome was to determine whether the combination of OK lens and 0.01% atropine intervention are superior to OK lens, in terms of preventing myopia progression, by evaluating the axial length elongation in these two groups of participants. For the primary outcome analysis, the myopia progression over 2 years would be determined by the difference in axial length between the baseline and 24-month visit. Other measurements obtained at the follow-up visits were considered as secondary outcome measures.

### Secondary outcome

The secondary outcome was the comparison of the elongation of axial length between the combination of OK lens and 0.01% atropine group and OK lens group after 1 year. The change of pupil size and refraction between the baseline and 24-month visit will also be calculated as the secondary outcome. In addition, the safety was evaluated through the corneal endothelia cell and ocular surface function in these two groups of participants at each follow-up visit.

### Sample size calculation

The two-sample *t* test for superior statistical analysis was used for the sample size calculation. The parameters used for the sample size calculation included the following: a significance level of 0.05, 95% confidence interval, 80% power, and 1:1 allocation. According to previously published articles, the axial length elongation in the combination of OK lens and 0.01% atropine group was preset at 0.09 ± 0.12 mm, while the OK lens was preset at 0.19 ± 0.15 mm in 1 year [24]. According to the previous experience of the investigators with clinical trials for treating myopia and other published data, the rate of participant loss to follow-up over 2 years was estimated to be 20%. Calculations, which were two-sided, were performed using the software, NCSS PASS 11. A total sample of 96 eligible children was required in the trial, with 32 participants being planned to be assigned to each of the three study sites.

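### The sample size rests on 1-year elongation figures while the primary outcome is 24-month elongation, so the stated 80% power is not established for the primary analysis

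*Protocol article*

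**What the plan says.** The Sample size calculation section of the protocol article uses a two-sample *t* test for superiority with "a significance level of 0.05, 95% confidence interval, 80% power, and 1:1 allocation", and the calculation is two-sided. The combination arm is planned at 0.09 ± 0.12 mm; for the comparator the text reads "while the OK lens was preset at 0.19 ± 0.15 mm in 1 year [24". The same paragraph allows for 20% loss over 2 years and arrives at 96 children, 32 at each of three sites. The Abstract gives 48 per group.

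Under Primary outcome, "the myopia progression over 2 years would be determined by the difference in axial length between the baseline and 24-month visit". The Secondary outcome section lists the between-group comparison of elongation after 1 year.

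The Background cites a randomised trial of the same comparison in which the combination was "more effective in slowing axial elongation than monotherapy of OK lens over the 2 years (0.29 mm vs. 0.40 mm"). It notes that such earlier studies did not mask participants and gave the control group no placebo drop. No SD is quoted for that result.

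**The concern.** The planned difference and SDs belong to a time point at which the trial makes a secondary comparison. Only the loss rate refers to the 24-month horizon, so one calculation mixes two time frames. Both the treatment difference and the spread of axial elongation can change between 1 and 2 years, and power depends on their ratio. Nothing in the article says how either is expected to change.

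What is at stake is how the 24-month result is read. If the confidence interval includes zero, readers will take the finding to come from a trial with 80% power for its primary outcome. The article has not made that calculation.

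**Working it through.** **Inputs.** From Sample size calculation: means 0.09 and 0.19 mm (difference 0.10), SDs 0.12 and 0.15, two-sided 0.05, 80% power, 1:1 allocation, 20% loss, N = 96. From Background: 0.40 − 0.29 = 0.11 mm at 2 years. The 2-year SD is not given and is varied below.

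**Step 1: the plan's own figure.** Root-mean-square SD = √[(0.12² + 0.15²)/2] = √0.01845 = 0.136 mm.

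- Normal approximation: n per arm = 2(1.96 + 0.842)² × 0.01845 / 0.10² = 29. The *t* test gives 30 with equal variances and 31 with the Welch form.
- Dividing by 0.8 for loss gives 37 to 39 per arm, or 74 to 78 in total, not 96.
- With SD 0.15 in both arms, the *t* test gives 37 per arm; 37/0.8 rounds up to 47, or 94 in total. That is close to 96 = 3 × 32, but the article does not say that this was done.

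**Step 2: power at 1 year with the actual N.** Evaluable per arm = 48 × 0.8 = 38.4, taken as 38. The standard error of the difference is SD × √(2/38) = 0.2294 × SD. With SD 0.136 this is 0.0312, and the noncentrality is 0.10/0.0312 = 3.21 on 74 degrees of freedom. Power is 89%.

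**Step 3: a range for the 2-year SD.** If growth in each year has the same SD and the two years correlate at ρ, the 2-year SD = 1-year SD × √[2(1 + ρ)]. This is an assumption.

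- ρ = 0: 0.136 × √2 = 0.192 mm.
- ρ = 1: 0.136 × 2 = 0.272 mm.
- An unchanged SD of 0.136 corresponds to ρ = −0.5.

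**Step 4: power at 24 months**, 38 per arm, two-sided 0.05, noncentral *t*, with noncentrality = difference / (0.2294 × SD):

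| Difference (mm) | 2-year SD (mm) | Noncentrality | Power |
|---|---|---|---|
| 0.11 | 0.136 (unchanged) | 3.53 | 94% |
| 0.11 | 0.169 | 2.84 | 80% |
| 0.11 | 0.192 (× √2) | 2.50 | 69% |
| 0.11 | 0.272 (doubled) | 1.77 | 41% |
| 0.20 | 0.192 | 4.54 | 99% |
| 0.20 | 0.272 | 3.21 | 89% |

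At 0.11 mm the break-even SD is 0.169 mm, which is 24% above the 1-year value (0.169/0.136 = 1.24). Under the Step 3 model this corresponds to ρ = 1.546/2 − 1, or about −0.23.

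**Step 5: difference detectable with 80% power.** Noncentrality of 2.84 is needed, so the difference is 2.84 × 0.2294 × SD: 0.125 mm at SD 0.192 and 0.177 mm at SD 0.272.

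**The case against.** A reader might go further and infer that the trial is underpowered, because the cited 2-year difference of 0.11 mm barely exceeds the 0.10 mm planned at 1 year. The documents do not support that. The two figures come from different studies: the article gives no 1-year result for the study behind the 0.11 mm and no 2-year result for the source of the 0.10 mm. No study shown there reveals how the effect develops in the second year. Setting the planned 53% relative reduction (0.10/0.19) against the cited 27.5% (0.11/0.40) has the same weakness.

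Nor can a single low power figure be asserted. The 2-year SDs are assumed. An unchanged SD, or a difference that grows in proportion to the SD, would preserve or raise power. The 41% figure needs a doubled SD together with a difference of only 0.11 mm, and nothing in the article supports that pairing in particular.

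Three further points are fair. The calculation was evidently meant for the 24-month trial, since it uses 2-year loss, so it should not simply be relabelled as a calculation for the secondary outcome. On the printed SDs, 96 children are more than 1 year would require, which leaves some slack; the powers above already count it. The primary analysis is an ANCOVA adjusted for centre and reports a 95% confidence interval. That may gain some precision, by an amount that cannot be judged here, and the interval will show the precision achieved.

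These points limit what can be said about the direction and size of the error. None supplies the missing step from 1 year to 24 months.

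**Conclusion.** The mismatch stands on the article's own text: 1-year inputs, a 24-month primary outcome and no bridge between them. The stated 80% power is therefore not established for the primary analysis.

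Whether true power is above or below 80% is open. At 0.11 mm it runs from 94% to 41% over 2-year SDs of 0.136 to 0.272 mm and falls below 80% once the SD exceeds about 0.169 mm. At 0.20 mm it is 99% at SD 0.192 and 89% at SD 0.272. These figures assume 38 evaluable children per arm, a common SD and a two-sample *t* test with no gain from covariates. The mismatch is certain; the power figures are scenarios. The test, the error rate and the sample are unaffected.

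**What to change.** In the Sample size calculation section:

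1. State that 0.09 ± 0.12 and 0.19 ± 0.15 mm are 1-year values, whereas the primary outcome is at 24 months.
2. Restate the power for the 24-month outcome, either with a 2-year difference and SD and their source, or with a reasoned case that the 1-year values are conservative.
3. Report power and the 80% detectable difference at about 38 per arm over a range of 2-year SDs. Include the cited 0.11 mm as one scenario, noting that it comes from an unmasked trial without placebo.
4. Say which SD was used to reach 96, since the two printed SDs give 74 to 78.

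Date the restatement as made after recruitment, so that it is not taken for the original planning basis. Recruitment is closed at 96, so no enrolment change follows. The cost is one paragraph and a stated power that may be less favourable.

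### The printed sample-size inputs require about 76 to 78 children at 80% power, not the 96 stated; the figures are inconsistent in the conservative direction

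*Protocol article*

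**What the plan says.** All the inputs are in the protocol article, Sample size calculation:

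- Test: a two-sample t "test for superior statistical analysis was used for the sample size calculation".
- Error rates and allocation: "a significance level of 0.05, 95% confidence interval, 80% power, and 1:1 allocation".
- Sidedness and software: "Calculations, which were two-sided, were performed using the software, NCSS PASS 11".
- Effect: "the axial length elongation in the combination of OK lens and 0.01% atropine group was preset at 0.09 ± 0.12 mm", against 0.19 ± 0.15 mm with the OK lens, both at 1 year.
- Loss: "the rate of participant loss to follow-up over 2 years was estimated to be 20" percent.
- Result: "A total sample of 96 eligible children was required in the trial", planned as 32 at each of three sites.

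The Abstract gives 48 per group. Randomization and masking gives stratification by center with a fixed block size of 4. The section mentions no conservative common SD, no rounding step and no margin beyond the 20% loss.

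**The concern.** The section prints a full set of inputs and a result, so the result should follow from them. It does not: the usual calculation stops well short of 96. A reader cannot tell from the article what power the trial was planned for, how the two SDs entered the calculation, or how loss was allowed for. These figures are normally carried into the results report, where a mismatch would be repeated. Too few children is not the issue here, since the stated number is larger than the inputs require.

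**Working it through.** **Inputs.** Difference 0.19 − 0.09 = 0.10 mm; SDs 0.12 and 0.15 mm; two-sided alpha 0.05; power 80%; 1:1 allocation; loss 20%.

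**Step 1: evaluable children per arm.** The normal approximation is n = (z₀.₉₇₅ + z₀.₈₀)² × (SD₁² + SD₂²) / difference².

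- (1.960 + 0.8416)² = 7.849
- 0.12² + 0.15² = 0.0144 + 0.0225 = 0.0369
- n = 7.849 × 0.0369 / 0.0100 = 28.96, so 29

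With the exact t distribution, power at 30 per arm is 0.8006 with pooled variance and 0.79998 with unequal variances (Welch). The t test therefore needs 30 per arm, or 31 if Welch is applied strictly.

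**Step 2: allow for 20% loss.**

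| Method | Evaluable per arm | Total, n / 0.80 | Total, n × 1.2 |
|---|---|---|---|
| Normal | 29 | 74 | 70 |
| t, pooled | 30 | 37.5 → 38 per arm, 76 | 72 |
| t, Welch | 31 | 38.75 → 39 per arm, 78 | 76 |

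None of these reaches 96. A one-sided test would need fewer still.

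**Step 3: rounding for sites and blocks.** Equal numbers at three sites in full blocks of 4 require a multiple of 12. The first multiple at or above 76 to 78 is 84 (28 per site), not 96 (32 per site).

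**Step 4: size of the gap.** 96 − 78 = 18 and 96 − 76 = 20; 18/78 = 23% and 20/76 = 26%.

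**Step 5: power that 96 gives on the printed inputs.** With 20% lost, 48 × 0.80 = 38.4, so 38 per arm. Power is 0.886 by the t test (0.894 by the normal approximation). With no loss, 48 per arm gives 0.946. For 96 to be what 80% power requires, loss would have to be 1 − 31/48 = 35% to 1 − 30/48 = 37.5%, not 20%.

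**Step 6: routes that do reach 96.** Each changes or adds to what is printed.

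| Route | Arithmetic | Departure from the text |
|---|---|---|
| 90% power, inflation × 1.2 | 40 × 1.2 = 48 per arm, 96 | Power is stated as 80% |
| Loss applied twice | 30/0.8 → 38; 38/0.8 = 47.5 → 48 per arm, 96 | One 20% loss is stated |
| SD 0.15 in both arms | 37 per arm; 37/0.8 = 46.25 → 47; total 94, then 96 as a multiple of 12 | SD 0.12 is stated for one arm; rounding is not mentioned |
| Two-sided alpha 0.025 | also 94, then 96 as a multiple of 12 | Alpha is stated as 0.05 |

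**The case against.** The strongest reply is that 96 can be reached with the stated 80% power and 20% loss intact. A planner may take the larger SD, 0.15 mm, as a cautious common value, obtain 37 evaluable per arm and 94 after loss, and round up to 96 so that each of three sites holds eight full blocks of four. At SD 0.15 in both arms, 38 evaluable per arm gives 81.8% power, close to the stated 80%. The article condenses protocol version 1.0, which may record such a step.

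This stands as a possibility, and it rules out a reading that a reader might easily adopt: that the trial must really have been planned at 90% power, or that loss must have been counted twice. The documents support neither as the explanation. For the same reason they do not show that 96, or 80%, is itself the erroneous figure. The route does not remove the inconsistency, however, because it sets aside the 0.12 mm printed for the combination arm and relies on rounding the section does not mention.

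It is also fair to reply that the discrepancy is conservative, that all 96 children are already recruited (Trial status), that no interim analysis or stopping rule is planned (Data collection, management, and monitoring), and that no analysis set or model in Statistics analysis depends on the figure. All of that stands, and it limits the severity.

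**Conclusion.** The point holds as an inconsistency of minor to moderate weight. The printed inputs require 30 to 31 evaluable children per arm, about 76 to 78 in total or 84 with full blocks at equal sites, and not 96. With 20% loss, 96 gives about 89% power on those inputs. This rests on the test the section names, the two SDs as printed and a single 20% loss. The choice among normal, pooled t and Welch methods, and between the two ways of inflating for loss, moves the total only between 70 and 78.

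Two further inferences should be resisted. The trial is not underpowered on its own inputs. Nor can the surplus be read as deliberate cover for the 24-month endpoint: the inputs are 1-year elongation, the primary outcome is the 24-month change (Primary outcome), and the sample-size section claims no such margin. The 89% is therefore a figure for the 1-year difference, which is a secondary comparison, and it says nothing about power at 24 months.

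**What to change.** Retrieve the PASS 11 output and restate the paragraph with the power, SD or SDs, loss inflation and rounding actually used, so that a reader following it arrives at 96. If the printed inputs are the ones used, replace the claim that 96 was required for 80% power with a statement that 96 with 20% loss gives about 89% power for the 1-year difference. In either case, say plainly that this is not the power for the 24-month primary outcome. The cost is a text correction only; recruitment is complete, and neither the design nor the analysis changes.
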